#### 2.1.8. Intervention

***Active.*** The medical specialist inserted a small CH14-18 catheter into the rectum and gently administered a total amount of 150 cc of O_2_-O_3_ mixture at the concentration of 30 µg of O_3_ per cc of O_2_ over a 5–10 min period while the patient was laying on his/her left side. The patient was asked to refrain from passing gas or having a bowel movement for at least 30 m. This procedure is known as rectal insufflation. It was performed for 3 sessions/week (5 weeks). By the same approach, subjects were insufflated with 150 cc of pure O_2_.

***Placebo.*** By the same methodology and times and sessions, 150 cc of air was insufflated as a placebo treatment. 

#### 2.1.9. Data Collection

***Neuropsychological batteries*.** All participants were tested at each visit with the Mini Mental State Examination (MMSE) [33] to assess the global cognition, and several cognitive tests were selected to assess a broad range of cognitive abilities: RAVLT, immediate and delayed recall, ROCF Recall, TMT-A, TMT-B, ROCF copy, action and object naming subtests from the Battery for the Assessment of Aphasic Disorders (B.A.D.A), Raven’s Colored Progressive Matrices (CPM47), the Free and Clued Selective Reminding Test (FCSRT), and the Face–Name Association task (FNAT) [34]. In addition, baseline assessment (time = T0) included the administration of a digit span forward and digit span backward test. Story recall, phonemic verbal fluency (FPL) and semantic verbal fluency (FPC) tasks, the Token Test Auditory sentence comprehension subtest from BADA, and the De Renzi ideomotor apraxia test (right and left upper limb) were also used [35]. 

***Biological measures*.** Fasting venous blood samples were collected in the morning at the baseline (T0) and at follow-ups T3, T9, and T15 for the evaluation of alterations/modulations at the molecular level before and after treatment. 

**Proteomic analyses.** We used anticoagulant-free tubes and EDTA tubes to collect serum and plasma samples, respectively. Serum tubes were kept at room temperature for 1 h followed by 1 h at 4 °C before serum separation by centrifugation (2000× *g* for 10 min). Plasma tubes were immediately centrifuged at 2000× *g* for 10 min. Both serum and plasma samples were stored at −80 °C until the time of the assay. 

An assay was also performed for C-reactive protein (CRP) on serum samples from each subject at time T0.

**Mass spectrometry.** To extract metabolites, frozen serum samples were thawed at 4 °C, and 145 µL samples were transferred into 1.5 mL low protein binding tubes. Then, 5 µL of ESI Tuning Mix and 300 µL of extraction solvent (ACN, acetonitrile) were added to 145 µL of serum sample, mixed by vortex for 30 s, and centrifuged at room temperature and 13,000 rpm (15,871× *g*) for 10 min. Then, ~400 µL supernatant samples were transferred into 1.5 mL low protein binding tubes, and the extracts were dried in a vacuum concentrator at 30 °C. Sample-dried pellets were stored at 4 °C overnight (16 h) and reconstituted the next day prior to analysis. For reconstitution, 50 µL of ACN/H2O (20:80, *v*/*v*) was added to the pellet, mixed by vortex for 60 s, and then transferred to vials for LC-MS analysis. A procedure blank was generated identically without serum and used later to remove the background ions. Equal volumes of serum from all biological test samples were pooled as the quality control (QC) sample for the UHPLC–QqTOF–MS analysis. The QC samples were used to assess the reproducibility and reliability of the LC–MS system and to determine the repeatability of a metabolite feature.

**Transcriptomic analyses.** Peripheral blood samples were collected in PAXgene Blood RNA Tubes (PreAnalytiX, Qiagen, Valencia, CA, USA) and stored at −80 °C before RNA extraction. Total RNA was isolated according to the manufacturer’s instructions. The NanoDrop 2000 Spectrophotometer (Thermo Fisher Scientific, Waltham, MA, USA) was used for assessing RNA purity, and 260/230 ratios were evaluated. The Agilent 2100 Bioanalyzer by Eukaryote total RNA 6000 nano Kit (Agilent Technologies, Santa Clara, CA, USA) was used to determine concentrations and integrity. Samples with an integrity value lower than 7.0 were deleted.

#### 2.1.10. Data Management

The study investigators had accessibility to data collection forms and protocols in a secured shared drive. Moreover, they entered the data collected at the visits electronically, and then, the PI checked these data. The participant data were protected by password, so that all information remained confidential, and only study investigators had access to these data.

In addition, participants have been identified by a coded identification number that, to maintain participant confidentiality, has been used to identify all laboratory specimens, data collection, and administrative forms. The study coordinators and PI had access to the final trial dataset. The PI oversaw intrastudy data sharing.

#### 2.1.11. Data Monitoring

All aspects of data monitoring were overseen by the study coordinators with the assistance of the PI. Moreover, we expected subjects to be exposed to minimal risks during participation in this trial; thus, no interim analyses have been performed.

#### 2.1.12. Statistical Analysis

***Sample size*.** The power analysis was performed by the analysis of the univariate linear regression test. Using the accuracy of the model IFI scale as a multiple partial coefficient (R^2^) and the neuropsychological tests as fixed predictors, we found a power effect of 0.92 related to our population of 76 subjects. Similar findings (power effect of 0.80) were found when we considered the SHARE-Fit scale.

### 2.2. PART 2

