## Abstract

Cognitive frailty (CF) is a heterogeneous syndrome that is becoming one of the most serious health problems as the world’s population age is increasing. Elucidating its biological mechanisms as well as prevention and treatments is becoming increasingly significant, particularly in view of the associated health costs. We presented the study protocol of a research project funded by the Italian Ministry of Health (grant number RF-2016-02363298) aiming to investigate the cognitive and neuropsychological effects of a 5-week treatment with therapy based on the regenerative properties of ozone (O_3_) in a cohort of subjects stratified according to CF scores. We also studied the potential effects of O_3_ on blood-based biomarkers indicative of specific biological systems that may be altered in CF. Seventy-five older persons were recruited and randomly assigned to receive the active treatment (150 cc of oxygen-O_2_-O_3_ mixture at the concentration of 30 µg of O_3_ per cc of O_2_), O_2_, or the placebo (air) for 5 weeks. The main endpoints were the change in the scores of clinical scales from baseline (T0) to weeks 3 (T3), 9 (T9), and 15 (T15) after treatment and the change in biomarker levels resulting from transcriptomics, proteomics, and metabolomic patterns at the same times. The positive results from this study could have important clinical implications.

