## 2. Materials and Methods

The study is a randomized, double-blind, placebo-controlled, 5-week trial to assess the cognitive, neuropsychological, and biological effects of O_2_-O_3_ therapy on 75 older adults stratified according to CF scores. The study is being performed at the IRCCS Centro San Giovanni di Dio Fatebenefratelli, Brescia, Italy. In Table 1, we show the activities and timelines of the study.

As this is an ongoing trial, we divided this section into two parts where we specify what steps have been performed (PART 1) and what steps will need to be performed (PART 2).

### 2.1. PART 1

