#### 2.1.4. Study Schedule

In Figure 1, the study schedule of the following trial protocol is shown.

Participants were invited to undergo a face-to-face clinical assessment and neurocognitive batteries. In addition, subjects were asked about their socio-demographic status, their lifestyle, and their diet habits. Body Mass Index (BMI) was calculated too. The Everyday Memory Questionnaire (EMQ) was administrated to evaluate the presence of Subjective Memory Complaints (SMCs), whereas the Cognitive Reserve Index questionnaire (CRI-q) was used to measure cognitive reserve. Symptoms of depression were evaluated with the Geriatric Depression Scale (GDS), whereas physical health in general was estimated by the number of chronic diseases, by the Cumulative Illness Rating Scale (CIRS index), and by the number of drugs. Moreover, functioning skills in daily life were valued through the Barthel Index for Activities of Daily Living (Barthel index), Tinetti, and Instrumental Activities of Daily living (IADL) scales, in order to investigate the functional impact of any cognitive difficulties. Finally, an assessment of physical activity in daily life was performed. 

Specific scales/tools were used to assess the frailty status: the “Italian Frailty Index” (IFI) [31], an Italian version of the frailty index based on the accumulation of age-related deficits; the Frailty Instrument (FIt) for primary care based on the Survey of Health, Aging and Retirement in Europe (SHARE-FIt) [32], valuating five items (i.e., grip strength and four self-reported items: fatigue, loss of appetite and/or eating less than usual, difficulties climbing stairs and/or walking 100 m, and low level of physical activity); and the CDR scale to quantify the severity of symptoms of dementia.

A baseline neuropsychological visit, scheduled within a mean of 20 days of the face-to-face clinical assessment, was administered to all eligible participants, who were then allocated to one of the three intervention groups. A blood sample was collected for biomarker measurement from all subjects. Follow-up neuropsychological visits included (i) a visit 3 months after treatment (T3); (ii) a midpoint visit 9 months after treatment (T9); and (iii) an endpoint visit 15 months after treatment (T15). In each follow up, we collected blood samples for biomarker measurement.

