These -omic approaches along with bioinformatics will allow the identification of new molecular systems involved in the etiopathogenetic mechanisms of CF and potentially new mechanisms of action for the O_3_.

This ongoing trial has some strengths. The first is the length of the study: considering the three follow-up visits in the 15 months after treatment, it was long enough to expect to have more evidence on the trajectory of cognitive changes. Second, in this study, we will include an -omics biological corollary that will permit us to potentially identify new biomarkers associated with the response to treatment with O_2_-O_3_ therapy. Moreover, this will allow us to deepen possible new mechanisms of action of the O_3_ underlying the proposed treatment-associated benefits on cognition. On the other hand, although our sample has a power effect of 0.92/0.80, the results we will obtain should be confirmed in a larger population.

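### The only power figure (0.92/0.80) is for regressing frailty scores on neuropsychological tests; no power for the comparison between arms is documented, yet the Discussion gives it as the sample's power

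*Protocol article*

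**What the plan says.** Section 2.1.12 holds the only power statement in the protocol article.

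- **Method:** "The power analysis was performed by the analysis of the univariate linear regression test".
- **Effect size:** an R-squared, described as follows: "Using the accuracy of the model IFI scale as a multiple partial coefficient". No value is given.
- **Predictors, N and result for IFI:** "the neuropsychological tests as fixed predictors, we found a power effect of 0.92 related to our population of 76 subjects".
- **Result for the second scale:** "power effect of 0.80) were found when we considered the SHARE-Fit scale".

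The Discussion, under the trial's strengths and limits, returns to the figure: "although our sample has a power effect of 0.92/0.80, the results we will obtain should be confirmed in a larger population".

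The trial itself has a different target. Participants completed a baseline visit, "who were then allocated to one of the three intervention groups" (section 2.1.4). The primary endpoint is change in IFI or SHARE-FIt from baseline to T3, T9 and T15 (section 2.1.7). The longitudinal analysis has time and treatment as fixed factors (section 2.2.2).

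The sample is 75 elsewhere. The Abstract has "Seventy-five older persons were recruited and randomly assigned to receive the active treatment", and section 2 describes the "biological effects of O_2_-O_3_ therapy on 75 older adults stratified according to CF scores".

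**The concern.** A power statement under Sample size in a randomised trial is read as the chance of detecting a treatment effect. This one answers another question: whether neuropsychological scores explain variation in frailty scores. That power can be high or low whatever the treatment does, because treatment is not in the model.

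The Discussion widens the problem. Section 2.1.12 at least names the regression. The Discussion drops that qualification and sets 0.92/0.80 beside the results to come. A null comparison between arms could then be read as a negative finding from a trial with 92% power, which nothing in the article supports.

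Two smaller points belong here. The R-squared appears to come from the model fitted in the enrolled sample, which would make the figure observed power. And the power statement counts 76 people where the Abstract and section 2 count 75.

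**Working it through.** **1. The plan's own figure.** It can be neither reproduced nor refuted, because R-squared, the number of predictors and alpha are not given. One can ask what R-squared it implies. For the overall F test with p fixed predictors, the noncentrality is λ = N·R²/(1 − R²), with p and N − p − 1 degrees of freedom. With N = 76 and alpha assumed 0.05:

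| Predictors p (assumed) | R² for power 0.92 | R² for power 0.80 |
|---|---|---|
| 1 | 0.133 | 0.096 |
| 5 | 0.200 | 0.154 |
| 12 | 0.263 | 0.211 |
| 20 | 0.320 | 0.262 |

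Twelve is a count of the test scores that section 2.1.9 lists for every visit. Worked line: p = 5 and R² = 0.20 give λ = 76 × 0.25 = 19 on 5 and 70 df, power 0.92. The stated values are attainable for the regression. Nothing in the formula refers to arms.

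**2. Inputs for a between-arm comparison.** From the article: 75 randomised, three groups, air as comparator. Assumed, because not stated: 1:1:1 allocation (75/3 = 25 per arm), two-sided 5%, one active arm against air, one scale at one visit. Dropout is mentioned in section 2.1.5 without a rate, so 20 per arm (25 × 0.8) serves as an illustration. The effect d is the difference in mean change divided by the SD of change.

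**3. Detectable difference.** Normal approximation: d = (z₀.₉₇₅ + z_power)·√(2/n).

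- n = 25, power 0.80: (1.960 + 0.842) × √0.08 = 2.802 × 0.283 = 0.79. Noncentral t: **0.81**.
- n = 25, power 0.92: (1.960 + 1.405) × 0.283 = 0.95. Noncentral t: **0.97**.
- n = 20, power 0.80: 2.802 × √0.10 = 2.802 × 0.316 = 0.89. Noncentral t: **0.91**.

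**4. Power at assumed differences (noncentral t).**

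| d | 25 per arm | 20 per arm |
|---|---|---|
| 0.3 | 0.18 | 0.15 |
| 0.5 | 0.41 | 0.34 |
| 0.8 | 0.79 | 0.69 |
| 1.0 | 0.93 | 0.87 |

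At d = 0.5 the normal approximation needs 63 per arm for 0.80 and 91 per arm for 0.92.

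**5. Variants.**

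- Two comparisons with air at 0.025 each, 25 per arm: 0.90 SD for 80% power; power at 0.5 SD is 0.30.
- Three-arm F test, 25 per arm: λ = 75 × 0.25² = 4.69 at f = 0.25, power 0.46.
- Both active arms pooled, 50 against 25: 0.70 SD for 80% power; power at 0.5 SD is 0.52.

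**6. Baseline adjustment.** The article gives no baseline correlation ρ. In units of the follow-up SD, with equal variances, the change score has SD √(2(1 − ρ)) and the adjusted score √(1 − ρ²). For 80% power with 25 per arm:

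- ρ = 0.5: change 0.81 × 1.00 = 0.81; adjusted 0.81 × 0.866 = 0.70.
- ρ = 0.7: change 0.81 × 0.775 = 0.63; adjusted 0.81 × 0.714 = 0.58.

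So 0.81 SD of change must not be set beside 0.58 follow-up SD as if they shared a scale. At ρ = 0.7 the gain is from 0.63 to 0.58.

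**The case against.** Section 2.1.12 says openly what was powered. The regression also resembles a planned analysis: in section 2.2.2 the Automatic Linear Modeling step takes neuropsychological and biological values as inputs and IFI or SHARE-FIt as the target. The Discussion speaks of the sample's power without naming the comparison of arms. It calls the trial a pilot and asks for confirmation in a larger population. The full protocol (version 3.0, section 2.1.2) is not shown and may contain a derivation from a treatment effect.

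Much of this stands. The regression figure may be sound for that modelling step, and the pilot status softens the consequence. Several stronger readings that a reader might infer are not supported:

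- **That 0.92/0.80 is an arithmetic error.** The inputs needed to test it are not given.
- **That the trial is shown to be underpowered.** No target difference or SD is stated; the percentages above rest on assumed effects.
- **That 76 is wrong.** The regression needs no randomisation, so 76 and 75 could count different sets of people. They are unreconciled, no more.
- **That the power is certainly post hoc.** The wording suggests it but does not establish it.
- **That the sample size was never derived from a treatment effect.** The article cannot show this.

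What does not stand is the step from regression power to power of the sample. Neither the pilot label nor the planned modelling turns 0.92/0.80 into power for comparing arms, and this is not detail left to an analysis plan: the figure is printed and reused.

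**Conclusion.** The point holds in this form. The single power statement concerns an association between frailty scores and neuropsychological tests. No power for the randomised comparison is documented, and the Discussion presents the regression figure as the power of the sample.

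The practical gap is large across plausible settings. Only a difference of about 0.97 SD of the change score would give one active arm against air the power of 0.92 that a reader might assume. At half an SD the unadjusted power would be 41%, or 34% with 20 per arm. These values rest on assumed equal allocation, two-sided 5%, one scale, one visit and complete data. Baseline adjustment would improve them by an amount that depends on a correlation the article does not give.

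That the effect size came from the enrolled sample is an inference from the wording; the conclusion does not depend on it. The correction should be made, since this is the only sample-size justification in the article.

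**What to change.** 1. In section 2.1.12, state that 0.92 and 0.80 refer only to the regression of IFI and SHARE-FIt on the neuropsychological tests. Give the R-squared, number of predictors and alpha used, and say whether the R-squared was estimated in the enrolled sample.
2. In the Discussion, remove 0.92/0.80 as the power of the sample.
3. In its place, do one of the following:
   - State the detectable between-arm difference with every assumption labelled. For example: if 25 per arm complete, at two-sided 5%, for one active arm against air on one named scale at one named visit, power is 80% for 0.81 SD of the change score and 41% at 0.5 SD; with 20 per arm, 80% power needs 0.91 SD and power at 0.5 SD is 34%. Give any baseline-adjusted figure on a stated SD scale and for a range of correlations.
   - Or state that the trial is exploratory, with no formal power for treatment effects.
4. Reconcile 76 in section 2.1.12 with 75 in the Abstract and section 2, or say what each number counts.

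The cost is wording only, with no added participants. The stated power becomes less favourable.

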#### 2.2.1. Molecular Analyses

Blood sample material will be used to perform transcriptomic, proteomic, and metabolomic studies.

***Proteomic analyses*.** We plan to perform a cytokines and growth factors panel to be analyzed through automated the ELISA Platform (Bioplex, Biorad, Hercules, CA, USA).

***Mass spectrometry***.

**UHPLC–QqTOF–MS analysis.** Serum metabolic profiling analysis will be conducted using a UHPLC–MS system with a Bruker compact QqTOF MS (Bruker Daltonics, Billerica, MA, USA) and a Dionex UltiMate 3000 Rapid Separation LC (Thermo Fisher Scientific, Waltham, MA, USA) equipped with an Acquity UPLC BEH C18 (300 Å, 2.1 × 150 mm, 1.7 μm) column (Waters). MS parameters will be set up using microToF 3.4, ESI Compass 1.3, and HyStarPP 3.2 SR4 software (Bruker Daltonics, Billerica, MA, USA). A 10 µL aliquot of samples will be injected into the HPLC column, and elution will be performed at a flow rate of 0.4 mL/min using a gradient elution program as follows: 0 min, 5% B; 2 min, 5% B; 7 min, 40% B; 9 min, 80% B; 9.1 min, 100% B; 14 min, 100% B; 14.1 min, 5% B; 20 min, 5% B. The column temperature will be set up at 60 °C. The total running time will be 20.1 min. Mobile phase A will consist of 0.1% CH2O2 (formic acid) in H_2_O, while mobile phase B will consist of 96% EtOH. Ionization will be performed using an electrospray ionization (ESI) source, operating in positive mode. ESI source conditions will be set up as follows: capillary voltage, 4.0 kV; dry gas (N2) flow, 8.0 L min^−1^; dry gas (N2) temperature, 300 °C; nebulizer pressure, 3.0 bar. The mass scan range will be set from 200 to 950 *m*/*z*. The instrument will be calibrated prior to the analyses using 10 mM sodium formate.

**Data processing and analysis.** UHPLC–MS raw data files (.d) will be converted to mzML format using ProteoWizard (version 3.0.23339). The open-source MZmine 3 software (version 3.6.0) will be used to generate a peak table containing *m*/*z*, retention time (RT), and intensity for the peaks (also called features). Parameters for feature detection will be set up as follows: scan to scan accuracy, 0.005 *m*/*z*; minimum intensity, 1.0 × 10^3^; minimum peak width, 5 scans; minimum RT search range, 0.05 min; noise level, 1.0 × 10^2^. The retention time scan window will be limited to 5–15 min. In addition, 13C-related isotope peaks will be removed if peaks are ≤0.01 min apart, their *m*/*z* difference is ≤0.001 or 3 ppm, or if a monotonically decreasing trend in the isotope pattern is detected, retaining the most intense peak. The alignment of peaks and gap-filling will be performed by setting the following parameters: sample-to-sample *m*/*z* tolerance, 0.05 *m*/*z* or 50 ppm; RT tolerance, 0.4 min. Redundant peak entries due to misaligned feature list rows will be removed if two peaks are ≤0.05 min apart and their *m*/*z* difference is ≤0.05 or 10 ppm. Background peaks will be removed if the intensity in the biological samples is <3-fold of that in the procedure’s blank samples. Features not detected in at least 75% of QC samples will be excluded from the final table. The resulting peak table will be exported to a .csv file. Normalization of the dataset will be performed by applying the total intensity in an analysis (or sum of bucket values in analysis) normalization method. From the normalized data matrix, features with RSDs higher than 30% in the QC samples will be filtered out before proceeding with statistical analyses. We plan to perform a metabolic profile for each subject at baseline and after treatment.

***Transcriptomic analyses*.** We plan to perform gene expression profiling using the standard protocol for Agilent one-color gene expression microarray [36,37].

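### The metabolomic pipeline uses the pooled QC to assess and filter features but never to correct them, so feature-specific drift can stay in the data and cost precision

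*Protocol article*

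**What the plan says.** All references are to the protocol article.

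- **QC material and purpose (2.1.9, Mass spectrometry).** "Equal volumes of serum from all biological test samples were pooled as the quality control (QC) sample". Its purpose is then given: "The QC samples were used to assess the reproducibility and reliability of the LC–MS system and to determine the repeatability of a metabolite feature".
- **Run time and calibration (2.2.1, UHPLC–QqTOF–MS analysis).** "The total running time will be 20.1 min" for each injection. "The instrument will be calibrated prior to the analyses using 10 mM sodium formate".
- **Processing (2.2.1, Data processing and analysis).** The first QC filter is "Features not detected in at least 75% of QC samples will be excluded from the final table". After the peak table is exported, "Normalization of the dataset will be performed by applying the total intensity in an analysis". The second QC filter follows: "features with RSDs higher than 30% in the QC samples will be filtered out before proceeding with statistical analyses".
- **Tests (2.2.2).** Metabolites go to PCA and a univariate analysis of treatment. No term for injection order or batch is named.

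**The concern.** The QC has three uses: assessing the system, the 75% detection filter and the 30% RSD filter. All three judge features; none changes an intensity.

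The only intensity correction is total-intensity normalization, which applies one factor to everything in an injection. If one feature loses signal over the run while another gains, that factor cannot put both right. The other candidates do not fill the gap. Calibration is described only as preceding the analyses. The tuning mix added to each sample (2.1.9) is not used for normalization in 2.2.1.

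Because the RSD is computed after normalization, the drift it tolerates is what normalization left behind. That drift goes into the metabolite comparisons with about 25 people per arm (75/3). The repeated QC injections would reveal the trend, but the plan does not use it.

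**Working it through.** The plan states no drift or metabolomic precision figure, so there is nothing of its own to reproduce.

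**Inputs from the article.** RSD limit 30%; 20.1 min per injection; 75 participants (the sample-size paragraph says 76); blood at T0, T3, T9 and T15.

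**Assumptions.** Drift is linear over the run. Biological CV is 30–50%, within-person correlation (ρ) 0.5–0.7, and random analytical RSD (r) 10–25%, with 15% as the working value. The article gives none of these.

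**1. Drift that the filter lets through.** Linear drift with total range D (as a share of the mean) over evenly spaced QC injections has SD D/√12. With random RSD r, a feature passes if D²/12 + r² ≤ 0.30², so the largest D is √(12 × (0.09 − r²)).

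| Random RSD | Largest D |
|---|---|
| 0 | 0.30 × √12 = 1.04 |
| 10% | √0.96 = 0.98 |
| 15% | √0.81 = 0.90 |
| 20% | √0.60 = 0.77 |
| 25% | √0.33 = 0.57 |

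The value 1.04 is a ceiling that needs no random error and many QC injections. Without random error but with few QC injections, the sample SD gives 0.80 for 6 and 0.89 for 10. A single mid-run step is limited to 0.60.

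**2. Run time.** Section 2.2.1 plans a profile at baseline and after treatment, which may mean two per participant; Table 1 lists molecular analyses at four times.

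- Two profiles: 75 × 2 × 20.1 / 60 = 50.25 h.
- Four profiles: 75 × 4 × 20.1 / 60 = 100.5 h.

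Both exclude QC and blank injections. The limits in step 1 do not depend on run time.

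**3. Precision with mixed injection order.** The variance of a within-person change is multiplied by

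1 + (D²/12) / [CV²(1 − ρ) + r²], with r = 0.15.

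- Largest denominator (CV 0.5, ρ 0.5): 0.125 + 0.0225 = 0.1475.
- Smallest denominator (CV 0.3, ρ 0.7): 0.027 + 0.0225 = 0.0495.
- D = 0.50: D²/12 = 0.0208, ratio 1.14 to 1.42. Then 25 per arm act like 25/1.42 ≈ 18 to 25/1.14 ≈ 22.
- D = 0.90 (the filter limit at 15% random RSD): D²/12 = 0.0675, ratio 1.46 to 2.36. Then 25 per arm act like about 11 to 17.

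**4. Bias between arms.** A simulation used 25 per arm, four visits, between-person CV 40%, within-person CV 20%, drift at the 104% ceiling and 4,000 runs. Type I error of the arm comparison was 4.6–4.7% with random order and 4.6–5.2% with samples blocked by visit. In a separate two-arm simulation with random order, power for a change contrast fell from 81% to 29%. That is the ceiling case with no random analytical error, so it bounds the loss and is not an expected value.

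**5. Before-after comparisons.** Only if samples run in visit order does drift shift a before-after mean. With two blocks the shift is D/2, or 0.45 at D = 0.90. With four blocks it is D/4 = 0.23 from T0 to T3 and 0.75 × D = 0.68 from T0 to T15.

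**The case against.** The strongest reply is that this is an omission in a condensed article. Injection order, QC spacing and batch layout belong in a laboratory procedure, and a correction step may be there too. For run order and batches that reply stands, and their absence is not held against the plan. It is weaker for the correction step: section 2.2.1 writes the chain out to the level of m/z tolerances and goes from normalization to RSD filter to tests. A correction added elsewhere would alter that published sequence.

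Second, no document shows that drift occurs, and one linear trend over a continuous run is an assumption. Overnight storage of the dried pellets would also fit processing in sets. This stands, so the figures are limits on what the filter tolerates, not forecasts.

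Third, a reader might infer that uncorrected drift biases the treatment comparison. The article does not support that. Simulated type I error rose clearly only when run order was tied to arm, and only in tests of levels: 26% at T3 with arms blocked within visit, against 4.7% for the change test. Nothing in the article suggests such an order.

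Fourth, the stake is limited. Section 2.1.7 defines the secondary endpoint as RNA and proteins; the Discussion adds metabolomics and calls the trial a pilot. The stated power of 0.92 and 0.80 concerns the frailty scales and is unaffected.

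**Conclusion.** The point holds as a matter of precision. As written, the pipeline assesses and filters on the QC but never corrects with it, and its one factor per injection leaves feature-specific drift in the retained features. The tolerated linear drift is about 57–98% of the mean for random RSD of 25–10%. The variance of a change rises by a factor of about 1.1–1.4 at 50% drift and 1.5–2.4 at the limit, under the assumed CVs, correlations and 15% random error.

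Two stronger readings go too far. Drift of 104% is a ceiling, not an expected amount. A run of 100 hours is one reading of the sampling plan; 50 hours is the other. Uncontrolled before-after comparisons could be shifted, but only if samples ran in visit order, which the article does not say. The change is worth making because it is cheap and the arms are small.

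**What to change.** In section 2.2.1, add one step after total-intensity normalization and before the RSD filter. For each feature, fit the trend over injection order on the QC injections (for example QC-based LOESS or a spline, within batch) and divide all intensities by it. Then apply the 30% limit to the RSD of QC injections left out of that fit, so that the filter does not reward overfitting.

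If QC injections are few, a flexible curve may overfit. In that case use a simple low-order trend, or enter injection order and batch as covariates in the univariate model of section 2.2.2.

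The cost is an analysis script. The QC pool already exists and the metabolomic analysis is in Part 2, still described as planned. If samples have already been run, the correction still works provided QC injections were spread across the run. The sponsor should also confirm that injection order was or will be randomised with each participant's samples in one batch; this is a request for confirmation, not part of the finding.
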